#### Secondary outcomes.

For the secondary outcomes, we will gather data on instrumental activities of daily living (IADL) and quality of life (QoL) to gain further insights into the participants’ overall well-being throughout the intervention. These secondary outcomes will be measured at both baseline and 12 weeks following the intervention. IADL will be assessed using the Lawton-Brody Instrumental Activities of Daily Living Scale, which evaluates independence in various functions like managing finances, taking medications, and handling transportation (Lawton & Brody, 1969).

To assess quality of life, the EQ-5D-5L questionnaire will be administered, a widely used tool for evaluating health-related QoL [31]. This tool has two parts: a descriptive system where participants rate aspects such as mobility, self-care, usual activities, pain/discomfort, and anxiety/depression on a scale from ‘no problems’ to ‘extreme problems.’ The second part, the EQ Visual Analogue Scale (EQ VAS), allows participants to indicate their general health on a vertical scale, ranging from ‘The best health you can imagine’ to ‘The worst health you can imagine.

### Data collection and monitoring

Data collection and monitoring of participants’ progress will be conducted by trained research assistants who are physiotherapy students or qualified physiotherapists. While the delivery of the intervention will be done by the main researchers (First and third author) assisted by the research assistants. Before participant recruitment, to ensure consistency across different settings, the research assistants will undergo thorough training, including understanding the protocol of the PTICOPE and hands-on practice with all outcomes measures for measuring the IC, guiding participants through tailored exercises, and providing education on self-management strategies. The research assistants will also monitor progress, adjust interventions to individual needs with guidance from the main researchers.

Recruitment of study participants will be conducted at three PAWE after obtaining research ethics approval and permission from the person in charge of the centers. The researchers will invite all participants who are members of the PAWE via letter of invitation, flyers, and verbal invitations. Those who volunteer to participate will be invited to a briefing session to inform the purpose and procedure of the study. Participants who provided informed consent and fulfilled the inclusion criteria will undergo the 12-week RCT. All participants will undergo an evaluation of the sociodemographic data, and primary and secondary outcomes at baseline. Evaluation of primary outcomes will be repeated at week 4, week 8, and week 12. Evaluation of secondary outcomes will be repeated at week 12. Once baseline data has been collected, participants will be randomly assigned to either the intervention or control group. The intervention group will receive the PTICOPE module in the form of a workbook and include comprehensive guidance on its use to support IC. In contrast, the control group will receive general information on the importance of maintaining IC, along with health education on the importance of exercise, and healthy diet, and self-care management which include recommendations to seek relevant healthcare services based on their baseline IC measurements.

### Data analysis

All statistical analyses will be conducted using SPSS version 29, with a significance level set at p < 0.05. Data will first undergo cleaning and analysis in SPSS, where frequency distributions and graphical representations will be used to identify outliers and missing values. For normality testing of interval data, the Kolmogorov-Smirnov and Shapiro-Wilk tests will be applied. Descriptive analysis will be conducted for participants’ demographics and baseline characteristics to describe data using tables, averages, standard deviations, ranges, frequencies, and percentages. Where appropriate, statistical comparisons between the intervention and control groups will be conducted, utilizing the independent t-test for continuous data and the Chi-square test for categorical data.

To evaluate the intervention’s impact on the primary outcomes, a repeated measures ANOVA will be conducted after data collection, as the primary outcomes involve measurements at baseline, week 4, week 8 and week 12, to evaluate the significant effects of time, intervention, and their interaction. For the secondary outcomes which involve measurements at baseline and week 12, the paired-t-test will be performed to determine the impact of the intervention.

The non-parametric tests will be performed if the main outcomes are not normally distributed that include the Friedman test and Wilcoxon signed-ranked test for the primary and secondary outcomes, respectively.

In the event of missing data due to participant dropout or incomplete data collection, an intention-to-treat (ITT) analysis will be employed to maintain the validity of the randomization process. Missing data will be managed using appropriate imputation techniques, depending on its nature and extent. For continuous variables, multiple imputation methods will be applied, while for categorical variables, methods such as last observation carried forward (LOCF) may be used. Sensitivity analyses will also be performed to assess the robustness of the results to the assumptions about the missing data.

To ensure data privacy and confidentiality, hard-copy forms collected from participants will be stored securely. All datasets will be digitized and saved on password-protected laptops, with backup copies maintained on password-protected USB drives and external hard drives. Access to these datasets is restricted to the principal researcher.

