Findings indicate that locomotion is the most commonly affected domain [9], and that IC decline is independently associated with increased risks of frailty, disability, falls, fractures, and immobility [10], suggesting that physiotherapy plays a critical role in maintaining and enhancing IC among older adults. Therefore, we aimed to develop a Physiotherapy-led Person-Centered Integrated Care for Older People (PTICOPE) program and evaluate its effectiveness in improving IC among older adults living in the community. We hypothesized that older adults participating in the PTICOPE program would experience significant improvements in their IC domain scores, including mobility, vitality, psychological function, cognitive function, hearing, and vision, compared with the control group. This community-based program is expected to empower older adults to achieve greater independence, enhance their functional abilities, and improve their overall well-being. Additionally, it provides guidelines for physiotherapists and other healthcare professionals working with community-dwelling older adults to regularly screen IC and monitor outcomes effectively.

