### Sample size determination

The sample size was calculated using G* Power 3 software for a repeated measures ANOVA (Baseline, week 4, week 8, week 12 measurements), aiming for a statistical power of 90%, an alpha level of 0.05, an estimated medium effect size (0.25), and a standard deviation of 2.5 for the primary outcomes and a correlation among repeated measures of 0.5. The selection of these parameters was guided by a previous study examining multicomponent exercise interventions in older adults to enhance, which reported a meaningful change of 1 point in the Short Physical Performance Battery (SPPB) as a clinically significant threshold [14].

Based on the initial analysis, a minimum of 60 participants is needed to detect a significant effect within each group. To account for potential attrition, such as participant dropouts due to withdrawal, health issues, or other factors, about 15 to 20% increase was applied. This adjustment results in a target sample size of 70 participants, divided equally into two groups (35 per group) to ensure the study maintains sufficient power to detect meaningful differences in IC changes between the intervention and control groups.

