### Outcome measures

#### Primary outcomes.

The repeated measures of the six domains of IC (cognitive decline, limited mobility [locomotor], malnutrition [Vitality], visual impairment, hearing loss, and depressive symptoms) are the primary outcomes of this study. These outcomes will be assessed at baseline and weeks 4, 8, and 12, using the WHO ICOPE screening tool. The ICOPE screening tool is a sensitive instrument to detect IC among community-dwelling older adults that does not require a substantial workforce [18]. It is used as the first step in each care pathway that covers all six core domains of IC to identify declines in IC across the six domains [19]. The psychometric properties of the ICOPE screening tools to assess IC domains among older persons from different settings have been reported in a few studies [20–22]. However, a systematic review found that the methods for assessing each of the IC domains differ substantially across studies and there is no consensus on the best method to compute an eventual global compound score to evaluate IC [23]. On the other hand, further improvements are needed in the vitality dimension of the ICOPE screening tool to enhance its sensitivity in identifying individuals at risk of malnutrition [24]. Hence, for this study, some measures of outcomes for the IC domains will be based on those validated in the Malaysian population.

We will use the validated Malay version of the Mini-Mental State Examination (MMSE) to measure cognitive function [25]. This tool includes items on orientation (5 points), registration (3 points), attention and calculation (5 points), recall (3 points), and language (9 points), with a maximum score of 30. A higher MMSE score indicates better cognitive function.

To assess locomotor or mobility function, we will use the Short Physical Performance Battery (SPPB) [26,27]. The SPPB comprises three components: gait speed (measured over 4 meters), lower limb strength (five-repetition chair rise), and static balance (side-by-side, semi-tandem, and tandem stands), with each component contributing up to 4 points. The total SPPB score ranges from 0 to 12, with higher scores indicating better locomotion.

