For vitality assessment in the ICOPE screening tool, we will use questions on unintended weight loss of more than 3 kg in the past three months and appetite loss. This study will employ the validated Malay version of the short-form Mini Nutritional Assessment (MNA) [28]. The MNA has a maximum score of 14, with higher scores indicating better nutritional status.

For hearing and vision assessments, we will follow previously reported procedures, using self-reported hearing and vision impairment [29]. Participants will be categorized as having total or severe loss (0 points), moderate loss (0.5 points), or normal to mild loss (1 point).

Psychological function, as indicated by depression level, will be assessed using the validated Malay short-form Geriatric Depression Scale (GDS-15) [30]. This scale consists of 15 items with “Yes” (1 point) and “No” (0 point) responses; a higher score indicates a greater level of depression.

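### The primary repeated measures ANOVA uses pre-randomisation baseline as an outcome level and names no treatment test; one prespecified, baseline-adjusted between-arm contrast would use the same data better

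*Protocol article*

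**What the plan says.** The Introduction of the protocol article sets a comparative hypothesis: participants in the programme "would experience significant improvements in their IC domain scores" relative to the control group. The Primary outcomes section takes as primary "The repeated measures of the six domains of IC", assessed at baseline and weeks 4, 8 and 12. It names no primary time point.

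The Data analysis section evaluates the intervention's impact on these outcomes by repeated measures ANOVA on "measurements at baseline, week 4, week 8 and week 12, to evaluate the significant effects of time, intervention, and their interaction", "with a significance level set at p < 0.05". Baseline is thus a level of the outcome, not a covariate. No term is named as the test of treatment.

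The Data collection and monitoring section places randomisation after baseline data collection. The Sample size determination section also assumes a four-measurement repeated measures ANOVA, with "a standard deviation of 2.5 for the primary outcomes and a correlation among repeated measures of 0.5". It refers to a study that "reported a meaningful change of 1 point in the Short Physical Performance Battery (SPPB) as a clinically significant threshold".

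**The concern.** A pre-randomisation measurement cannot carry a treatment effect. As a fourth outcome level it adds a zero to the average that the group main effect tests. Used as a covariate, the same measurement would remove variance from the comparison.

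The second problem is which result counts. Three effects are listed as bearing on the intervention's impact, and only two of them compare arms. A time effect can arise from practice, from regression to the mean, or from the health education that the control group also receives. The risk of misreading is real here, because the same section evaluates the intervention's impact on the secondary outcomes by a paired t-test, and its non-parametric fallback for the primary outcomes is the Friedman test. Both are within-group methods. The trial could report a significant time effect as success when the arms did not differ, or miss a real difference with an inefficient test.

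**Working it through.** **The plan's own figure.** The inputs are f = 0.25, alpha 0.05, power 90%, four measurements and correlation 0.5. The usual noncentral F calculation gives a total N of 30 for the interaction (λ = f²·N·4/(1−ρ)) and 108 for the group effect (λ = f²·N·4/(1+3ρ)). Neither is the stated 60. At N = 60 these give 99.8% and 67%. The mismatch is a separate matter. It matters here because the plan does not say which term was powered.

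**Inputs for the comparison.** From Sample size determination: difference 1 point, SD 2.5, ρ = 0.5, alpha 0.05, and 60 evaluable, so n = 30 per arm. Assumed, because the protocol gives neither: equal correlation between all visits, and three profiles of the arm difference at baseline and weeks 4, 8 and 12:
- constant: 0, 1, 1, 1
- linear: 0, 1/3, 2/3, 1
- waning to half: 0, 1, 0.75, 0.5

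**Dilution.** The four-visit mean difference is 3/4 = 0.75 (constant), 2/4 = 0.50 (linear) and 2.25/4 = 0.5625 (waning). In every case it is three quarters of the post-baseline mean (1, 0.667, 0.75).

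**Formulas, with numbers for the constant profile.**
- Group main effect: variance of a person's four-visit mean = SD²(1+3ρ)/4 = 6.25 × 2.5/4 = 3.906. λ = n·d²/(2·variance) = 15 × 0.5625/3.906 = 2.16, on F(1, 58).
- Interaction: λ = (n/2)·Σ(d_t − mean)²/[SD²(1−ρ)] = 15 × 0.75/3.125 = 3.60, on F(3, 174). The sum of squares is 0.556 for linear and 0.547 for waning.
- Baseline-adjusted mean of weeks 4, 8 and 12: variance = SD²[(1+2ρ)/3 − ρ²] = 6.25 × 0.4167 = 2.604. λ = 15 × 1/2.604 = 5.76, on F(1, 57).
- Baseline-adjusted week 12: variance = SD²(1−ρ²) = 4.6875. λ = 15/4.6875 = 3.20, on F(1, 57).

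| Profile (ρ = 0.5, 30 per arm) | Main effect | Interaction | Adjusted mean of weeks 4, 8, 12 | Adjusted week 12 |
|---|---|---|---|---|
| Constant | 30% | 32% | 66% | 42% |
| Linear | 16% | 24% | 35% | 42% |
| Waning to half | 19% | 24% | 42% | 14% |

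**Sensitivity to ρ.** Across ρ = 0.3, 0.5 and 0.7 with these three profiles (nine cases), the adjusted post-baseline mean beats both ANOVA treatment terms each time. The closest case is 45% against 39% for the interaction (ρ = 0.7, linear). The week-12 contrast does not always win: at ρ = 0.3 with a constant effect it has 36% against 38% for the main effect.

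**Outside those nine cases.** If the effect appears only at week 12 (0, 0, 0, 1; ρ = 0.5), the adjusted mean has 12% (λ = 15 × (1/3)²/2.604 = 0.64), against 32% for the interaction and 42% for week 12.

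**The time term.** Suppose both arms rise linearly by 0.4 SD to week 12 and do not differ. Then λ = 60 × 0.4² × 0.5556/0.5 = 10.67 on F(3, 174), and the time effect is significant with probability 78%.

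**The case against.** The strongest defence is that the ANOVA does contain a proper treatment test. The time-by-intervention interaction addresses the stated hypothesis directly, and baseline as a level does not dilute it. That stands. A reader might infer that the planned analysis cannot detect or fairly test the treatment effect. The protocol does not support that: the dilution affects the group main effect only, and the interaction loses power because its 3 df name neither a visit nor a direction.

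A reader might also infer that a week-12 baseline-adjusted comparison is always stronger. It is not. If the effect peaks at week 4 and halves by week 12, it has 14% power against 24% for the interaction. Waning is plausible because weekly meetings cover only the first four weeks, although the Limitations section promises weekly contact. Nor does the protocol make week 12 primary, so that would be a choice.

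Three further criticisms are tempting but do not hold:
- Loss of participants with a missed visit: the Data analysis section plans intention-to-treat, multiple imputation for continuous variables and sensitivity analyses.
- Dilution of vitality by a three-month recall item: "we will use questions on unintended weight loss of more than 3 kg in the past three months and appetite loss" describes the screening questions, and the next sentence names the short-form MNA as the measure employed.
- No centre term: this is detail that an article may leave to the full analysis plan.

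**Conclusion.** The point holds in limited form. The protocol fixes a primary analysis in which baseline is an outcome level, and lists three effects without naming the treatment test. The group main effect is cut to three quarters of the average post-baseline effect, which is 0.75 of the full effect if constant and 0.50 if linear. The interaction is valid but inefficient for sustained effects. The time effect is not a comparison of arms.

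Under the protocol's 1 point, SD 2.5 and ρ = 0.5, adjusting the post-baseline mean for baseline raises power from 24–32% (interaction) to 35–66% over the three profiles. This rests on those assumed profiles and on equal correlations, and it reverses for an effect confined to week 12. The direction of the gain is therefore well supported for sustained effects, while its size is not fixed by the protocol. It is a SHOULD-level change.

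**What to change.** For the continuous primary scores (MMSE, SPPB, short-form MNA, GDS-15), replace the ANOVA with a model of weeks 4, 8 and 12 containing arm, visit, arm by visit, and baseline score as covariate. Name in advance one between-arm contrast per outcome, reported with a 95% CI: the average over the three post-baseline visits, or week 12 if that is the time point of interest. For the three-level hearing and vision scores, use an ordinal analogue. State that change over time, in either arm or pooled, is not evidence of efficacy.

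The cost is a change of wording in the analysis plan; no additional measurements are needed. The contrast must be chosen before data are seen, and a wrong guess about the time profile costs power. The change does not rescue the sample size: even the best case above, 66%, is well short of the planned 90%.

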**Methods:**

This is a 12-week, multicenter, randomized controlled trial involving 70 community-dwelling older adults aged 60–75, recruited from three *Pusat Aktiviti Warga Emas* (PAWE) (Activity Center for Older Adults) in the Northern region of Malaysia. Participants will be randomized to either the intervention group, receiving the PTICOPE module workbook and guided use, or the control group, receiving general IC information, healthcare education, and self-care management. The recruitment of participants for this study has not yet commenced. Recruitment is expected to start after completing the validation of the PTICOPE module, however, it is anticipated that the recruitment start date is in February 2025 and will end in August 2025. Primary outcomes, including locomotor, psychological, cognitive, vitality, visual, and hearing functions using validated scales, will be collected at baseline, 4^th^, 8^th^, and 12^th^ week of the study period. Secondary outcomes will evaluate QoL, activities of daily living, urogenital health, and oral health at baseline and 12^th^ week. The normality of data will be checked. The independent t-tests, Chi-square tests, paired t-tests, and Repeated measures ANOVA will be used for data analysis, with a significant level at p < 0.05.

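### The test named for the secondary outcomes compares participants with their own baseline, and no between-arm test is assigned to IADL or EQ-5D-5L

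*Protocol article*

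**What the plan says.** The Secondary outcomes section of the protocol article defines two outcomes: "we will gather data on instrumental activities of daily living (IADL) and quality of life (QoL"), measured with the Lawton-Brody scale and the EQ-5D-5L. The abstract also lists urogenital and oral health. Assessment is at baseline and once more; the data collection section says "Evaluation of secondary outcomes will be repeated at week 12".

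The Data analysis section assigns the test and its purpose: "For the secondary outcomes which involve measurements at baseline and week 12, the paired-t-test will be performed to determine the impact of the intervention". If the data are not normally distributed, the replacements are the "Friedman test and Wilcoxon signed-ranked test for the primary and secondary outcomes, respectively".

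Two other statements in that section matter here. The primary outcomes get a repeated measures ANOVA "to evaluate the significant effects of time, intervention, and their interaction". Before that, directly after the sentence on describing demographics and baseline characteristics, comes a general statement: "Where appropriate, statistical comparisons between the intervention and control groups will be conducted, utilizing the independent t-test for continuous data", with Chi-square for categorical data. The abstract lists independent t-tests, Chi-square tests, paired t-tests and repeated measures ANOVA without tying any of them to an outcome.

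**The concern.** In a 1:1 parallel-group trial the effect of the intervention is a difference between arms. A paired t-test of week 12 against baseline asks only whether the average participant changed. It has no term for arm, and neither has the signed-rank test.

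Any change that would have happened without PTICOPE is therefore counted as its effect. Such change is plausible here. Controls receive an education session on exercise, diet and self-care, and advice to seek care based on their baseline results. They are also reassessed at weeks 4, 8 and 12 with reminders. Participants know their allocation, and EQ-5D-5L is self-rated. A claim about quality of life or daily function made from the named test would not rest on the randomised comparison. The Discussion and Conclusions name better quality of life and greater independence or functional ability among the programme's expected benefits.

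**Working it through.** **Step 1: what each named test contrasts**

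| Place in the protocol article | Test | Assigned to | Contains an arm contrast? |
|---|---|---|---|
| Data analysis, primary outcomes | Repeated measures ANOVA | Primary outcomes | Yes (intervention and interaction) |
| Data analysis, secondary outcomes | Paired t-test | Secondary outcomes | No |
| Data analysis, fallback | Wilcoxon signed-rank | Secondary outcomes | No |
| Data analysis, after baseline descriptives | Independent t-test, Chi-square | No outcome named | Yes |
| Abstract | Independent and paired t-tests, Chi-square, ANOVA | No outcome named | Mixed |

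No row both contains an arm contrast and is assigned to IADL or EQ-5D-5L.

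**Step 2: inputs for an illustration**

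- Significance level 0.05 (Data analysis section); two-sided is assumed.
- 35 per arm randomised (Sample size determination). The stated minimum of 60, read as a total, gives 60/2 = 30 completers per arm.
- Correlation 0.5. The sample size section gives this for the repeated primary measures; it is borrowed here.
- True intervention effect zero, with the same true change d in both arms. The documents give no value for d, so it is varied from 0 to 0.5 SD.

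The plan gives no operating figure for the secondary outcomes, so there is none to reproduce.

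**Step 3: false-positive rate of the paired test in the intervention arm**

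SD of change = SD × √(2(1 − 0.5)) = 1 SD. The paired t statistic then has n − 1 degrees of freedom and noncentrality d√n. At n = 30 the critical value is 2.045. For d = 0.3 the noncentrality is 0.3 × √30 = 1.643, which gives a rejection probability of 0.36.

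| Shared change d (SD) | n = 30 | n = 35 |
|---|---|---|
| 0 | 0.05 | 0.05 |
| 0.1 | 0.08 | 0.09 |
| 0.2 | 0.19 | 0.21 |
| 0.3 | 0.36 | 0.41 |
| 0.4 | 0.56 | 0.63 |
| 0.5 | 0.75 | 0.82 |

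**Step 4: the informal comparison of two within-arm results**

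The paired test might be run in each arm and the results set side by side. The chance of a significant improvement in the intervention arm with a non-significant result in the control arm is P(significant improvement) × (1 − P(significant)). At n = 30 and d = 0.3 this is 0.355 × (1 − 0.355) = 0.23. For d = 0, 0.1, 0.2, 0.3, 0.4 and 0.5 it is 0.02, 0.07, 0.15, 0.23, 0.25 and 0.19, with no intervention effect in any case.

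**Step 5: a between-arm test on the same data**

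The shared change d cancels in the difference between arms. In 20,000 simulated trials at each of d = 0, 0.2, 0.3, 0.4 and 0.5 (30 per arm), a two-sample t-test on change rejected in 4.7% to 5.2%.

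**The case against.** The strongest reply is that the general sentence on comparing the intervention and control groups by independent t-test may be meant to cover week 12 outcomes. It is not worded as limited to baseline, and the abstract names the independent t-test among the analysis methods. This stands in part. A reader might infer from the paired-test sentence that the randomised groups will never be compared on any secondary outcome; the documents do not support so firm a statement, because a two-sample test is available in the text. What they support is that none is assigned. The general sentence names no outcome, and the later sentence gives the secondary outcomes a different test for the express purpose of measuring impact. Even on the generous reading, that sentence names the wrong test.

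A second reply is that the error rates depend on an assumed shared change. That is correct. With no shared change the paired test rejects at 5%. The article says most members of the centres are independent in daily activities, so IADL may sit near its ceiling and leave little room for shared improvement. Participants are not selected for low scores on these outcomes, so regression to the mean should add little. The percentages illustrate the fault and should not be read as this trial's error rate.

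A third reply is that the hypothesis concerns the intrinsic capacity domains, whose ANOVA does compare the arms. That is true of the parametric primary analysis, which this point leaves untouched. It limits the damage to the secondary claims.

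Finally, this is not detail that an article may leave to a fuller plan. The article names a specific test for a specific purpose, and the test cannot serve it.

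**Conclusion.** The point holds. For the secondary outcomes the plan declares a within-person test, with a within-person fallback, as the measure of the intervention's effect, and assigns no between-arm test to IADL or EQ-5D-5L. This follows from the text alone and needs no assumption.

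The size does rest on assumptions: equal true change in both arms, approximately normal change scores, and a correlation of 0.5 borrowed from the primary-outcome calculation. On these, with 30 per arm, the false-positive rate runs from 5% with no shared change to 75% at 0.5 SD, against about 5% for a between-arm test.

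The fallback deserves equal attention, because a ceiling on IADL would make non-normal data, and so the signed-rank test, likely.

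**What to change.** Three edits to the Data analysis section:

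1. Replace the paired t-test with a between-arm comparison for each secondary outcome. The preferred form is ANCOVA of the week 12 score on arm, adjusted for the baseline score, reporting the adjusted difference and its 95% confidence interval. A two-sample test on change would also cure the fault. Adjustment for centre is optional, since the allocation described is a single shuffled sequence of envelopes without stratification.
2. Replace the Wilcoxon signed-rank fallback with a between-arm method, such as Mann-Whitney on change or rank ANCOVA. For the EQ-5D-5L dimensions, which are ordinal ratings, use an ordinal model with arm and baseline.
3. State that within-arm change is descriptive only.

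While that sentence is open, note that the Friedman test named there for the primary outcomes also lacks an arm term.

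The cost is a few sentences of text: no new data, visits or participants. The between-arm test will be less often significant than the paired one. For a true between-arm difference of 0.5 SD with 30 per arm and correlation 0.5, power is about 0.48 on change scores and 0.59 with ANCOVA, so the secondary results should be read mainly through their intervals.

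### The named non-parametric fallback for the primary outcomes, the Friedman test, has no group factor, so any primary outcome sent down that route would not be tested against control

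*Protocol article*

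**What the plan says.** The hypothesis at the end of the Introduction is that the intervention group will improve in its domain scores relative to control. The Data analysis section matches this at first: the primary outcomes, measured at baseline and weeks 4, 8 and 12, go into a repeated measures ANOVA examining time, intervention and their interaction, "with a significance level set at p < 0.05".

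The same section then sets a distributional switch. It states "For normality testing of interval data, the Kolmogorov-Smirnov and Shapiro-Wilk tests will be applied", and later "The non-parametric tests will be performed if the main outcomes are not normally distributed that include the Friedman test and Wilcoxon signed-ranked test", allotting the first test to the primary outcomes and the second to the secondary ones. No two-sample rank test, rank-based interaction test or ordinal model is named.

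Two of the six primary domains, hearing and vision, are three-level scores: "Participants will be categorized as having total or severe loss (0 points), moderate loss (0.5 points), or normal to mild loss (1 point"). The other four are bounded integer scales: SPPB (0 to 12), MMSE (maximum 30), MNA short form (maximum 14) and GDS-15.

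**The concern.** The switch is meant to protect against a distributional problem, but it also changes the question. The ANOVA interaction asks whether the arms change differently. Friedman asks whether scores differ across visits within the people analysed. Run on both arms together, it includes control data but never compares them. Run arm by arm, it gives two separate p-values, and one significant and one non-significant result is not a test of the difference. The protocol does not say which of the two is intended.

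Shared change over time is plausible here. Controls receive education on exercise, diet and self-care and are advised to seek services according to their baseline results (Data collection and monitoring), and everyone is measured four times. A significant Friedman result could then be read as evidence for the programme when there is none. A real difference between arms could also be missed.

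**Working it through.** **Inputs from the Sample size determination section.** "repeated measures ANOVA (Baseline, week 4, week 8, week 12 measurements"), so m = 4; planned power of 0.90 at a 5% level; for the effect, spread and correlation, "an estimated medium effect size (0.25), and a standard deviation of 2.5 for the primary outcomes and a correlation among repeated measures of 0.5"; and a cited study that "reported a meaningful change of 1 point in the Short Physical Performance Battery (SPPB"). One point is 1 / 2.5 = 0.4 SD.

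**The plan's own figure.** The stated minimum of 60 is not part of this point, but it shows that the inputs are read correctly. For the within-subject factor in one group, λ = f²·N·m / (1 − ρ) = 0.0625 × 30 × 4 / 0.5 = 15, with 3 and 87 degrees of freedom, which gives power 0.904. So N = 30, and twice 30 is 60. That is an inferred reading, consistent with the section's description of 60 as the number for an effect within each group.

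**Step 1: would hearing and vision fail a normality test?** Every possible split of n scores over 0, 0.5 and 1 was enumerated (excluding all values identical), and the largest Shapiro-Wilk p-value was recorded.

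| n | Largest p over all splits |
|---|---|
| 30 | 0.00011 |
| 35 | 0.000034 |
| 70 | 0.00000004 |

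Rejection at 0.05 is certain if these scores are tested, with no assumption about prevalence.

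**Step 2: would the bounded scales fail?** The protocol gives no means, so a range is needed. Rounded normal scores with SD 2.5, capped at the scale maximum, n = 35:

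| Scale | Assumed mean | Shapiro-Wilk rejects |
|---|---|---|
| SPPB-like (cap 12) | 7 | about 14% |
| | 8 | about 25% |
| | 9 | about 69% |
| | 9.5 | about 90% |
| MMSE-like (cap 30) | 25 | about 14% |
| | 26 | about 25% |
| | 27 | about 69% |

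Rates rise with n (SPPB-like, mean 8, n = 60: about 63%). Failure is likely near the ceiling and uncommon away from it.

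**Step 3: what does Friedman do when there is no arm difference?** Four correlated normal measures (ρ = 0.5), the same improvement in everyone by week 12, either linear or reached by week 4:

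| Shared improvement | n = 30 | n = 60 |
|---|---|---|
| 0.1 SD | about 6 to 7% | about 8 to 10% |
| 0.3 SD | about 19 to 25% | about 40 to 54% |

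A between-arm test would reject in about 5% throughout.

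**Step 4: Friedman against a between-arm rank test.** 35 per arm, SD 2.5, ρ = 0.5, linear trends (assumed), 4000 runs:

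| Change by week 12 (intervention / control) | Friedman, arms pooled | Friedman by arm: intervention only significant | Mann-Whitney on change |
|---|---|---|---|
| +1 / +1 | 76% | 24% | 4.7% |
| +1 / 0 | 23% | 41% | 35% |
| +1 / −1 | 4% | 25% | 88% |

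Row 1 has no treatment effect, yet pooled Friedman is usually significant. Row 3 has a true 2-point difference, yet pooled Friedman stays near its nominal level because the two trends cancel.

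**The case against.** Three points can be made for the plan.

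*Other between-arm tests are mentioned.* The Data analysis section allows an independent t-test or Chi-square test between groups where appropriate, the Abstract lists both for data analysis, and the fallback sentence is worded as a list that could be extended. A reader might therefore infer too much in saying that no between-arm test remains; the documents support only that no between-arm fallback is named. This softens the point without removing it. The t-test sentence directly follows the description of demographics and baseline characteristics and is not tied to the primary outcomes. A t-test is not what one turns to after normality fails, and a Chi-square test at one visit ignores baseline and the repeated measures.

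*Hearing and vision may never be tested for normality.* The testing sentence is limited to interval data, and these participants are put into categories. A reader might infer that the switch is bound to fire for these two domains. The text does not settle that, because the trigger sentence speaks more broadly of the main outcomes. If the two domains are exempt, a three-level score goes into ANOVA, which also needs correcting.

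*The simulated sizes rest on chosen values.* This stands. The failure rates for SPPB and MMSE and the rejection rates under shared improvement move widely with the assumed mean and trend, so ranges are given. That Friedman has no group factor needs no simulation.

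It would also be too strong to say that the fallback ignores the control arm. Pooled, it uses the control data but does not compare them with the intervention data.

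**Conclusion.** The point holds in this form: the protocol names, for its primary outcomes, a fallback that cannot test the hypothesis against control, and it names no between-arm alternative. This is a stated rule that does not fit the question, not a detail left to a fuller document.

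How many of the six domains are affected cannot be fixed from the protocol. Hearing and vision are affected if they are tested for normality. The other four are affected with a probability that depends on how close their scores lie to a scale limit. The false-signal rates above assume normal data with ρ = 0.5 and linear or early-step trends; Step 4 also uses the protocol's SD of 2.5.

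**What to change.** Delete the Friedman test as the fallback for the primary outcomes, and state that the primary contrast is between arms whatever the distribution.

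- **SPPB, MMSE, MNA, GDS-15:** keep the planned group-by-time comparison, or compare change from baseline by arm. Judge the model on its residuals, not on a normality test of raw scores. If they are poor, use a permutation test on arm, a bootstrap confidence interval, or Mann-Whitney on change from baseline.
- **Hearing and vision:** state an ordinal between-arm comparison from the outset, for example Mann-Whitney or an exact or permutation test on change. A proportional-odds model with baseline category is an option only if category counts allow. If the Introduction's review prevalences of 14.4% (hearing) and 17.9% (vision) carried over, which is an assumption because they come from a different screening measure, 60 participants would include only about 9 to 11 with impairment (0.144 × 60 = 8.6; 0.179 × 60 = 10.7), and the model could be unstable.
- **Secondary outcomes:** replace the Wilcoxon signed-rank fallback with a between-arm comparison of change. Deleting it alone would leave only the paired t-test, which is also a within-group test.

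The cost is a revision of the analysis wording and slightly more analysis work. Sample size, visits and data collection do not change.
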